#### Galactic cosmic radiation

The heavy ion component of cosmic radiation is potentially harmful for the CNS [40]. Studies have shown that exposing mice to a space radiation analog by directly irradiating them (100/150 cGy; irradiation duration ~2 min) adversely affects their memory and recognition, weeks to months post-exposure [41,42]. In addition, radiation exposure has been associated with acceleration of amyloid-β plaque pathology [41], which in itself is associated with an increased risk of Alzheimer’s disease in humans [43]. Nevertheless, the effects of cosmic radiation on the CNS are generally of greater concern for long-duration exploration missions (e.g. to the moon or Mars), and are less likely to result from short missions in low Earth orbit, where the Earth’s magnetic field is still protective against galactic cosmic rays, and in which the composition of these rays is less hazardous than beyond low Earth orbit [44].

#### Other risk factors

Other risk factors that may affect brain function that astronauts encounter, that are unrelated to the extraterrestrial environment, include stress, scarcity of resources [6], sleep loss, fatigue, circadian desynchronization, and work overload [12]. These can potentially be modeled with spaceflight analogs such as wintering over at Arctic field stations.

#### Multitude of risk factors

Determining the mechanisms behind the effects of spaceflight on the brain requires distinguishing the contribution of factors that are unique to the extraterrestrial environment from other characteristics of spaceflight. Currently, one of the risk factors that is expected to have a relatively large impact on brain structure and function during and after long duration spaceflight is the microgravity environment. To parse out the effect of microgravity from the overall effects of spaceflight, bed rest analog studies have been designed [45]–[47]. In these studies, participants are required to stay in bed with their heads tilted 6° below their feet for a number of consecutive days (see Figure 1). Under these conditions, the effects of microgravity such as unloading, reduced sensory inputs, and increased cephalic fluid distribution can be studied apart from other spaceflight effects on the brain. At this point, only two studies have investigated the effect of bed rest on cognitive functioning [48,49]. These studies have not revealed significant adverse cognitive effects of bed rest. However, their sample sizes were small (n = < 15) and cognitive functioning was measured with an extended cognitive screening instrument (i.e. WinSCAT, [50]), rather than with a thorough battery of neuropsychological tests. In addition, these studies have been conducted in healthy subjects that are generally able to compensate for small to moderate cognitive problems to a certain extent [51,52]. Up until now, only one study has investigated the effect of microgravity on brain activation during rest. This study by Liao et al. (2012) revealed a change in resting state connectivity of the left thalamus with a variety of brain cortical regions after a period of 72 hours of head down tilt bed rest [23]. This altered activation may potentially contribute to reduced motor control abilities in astronauts in a microgravity environment. Currently there are no studies that have investigated the association between bed rest, cognitive functioning, sensorimotor control, and brain function and structure.

**Figure 1 F1:**
[figure not shown]
Bed rest subject performing the Purdue Pegboard task.

### Study rationale and clinical relevance

Given the lack of data in humans, there is a fundamental gap in understanding the extent, longevity, and neural bases of long-duration spaceflight-induced changes in neurocognitive performance. Changes in brain structure and function may play a direct role in crew performance and thus operational success. Furthermore, it may impact the long-term health of astronauts, particularly in advanced age when the potential effects of spaceflight may interact with brain volume loss and functional reorganization that occurs with normal human aging [53-55]. NASA crewmembers may be at risk of accelerated aging effects if substantial volumetric degeneration and functional reorganization in the brain occurs during spaceflight. With the current study, we hope to identify the underlying neural mechanisms and operational risks of spaceflight-induced changes in behavior, and to identify whether a return to normative behavioral function following re-adaptation to Earth’s gravitational environment is associated with a restitution of brain structure and function or instead is supported by substitution with compensatory brain processes. Identification of neurocognitive changes occurring as a function of spaceflight is the first step towards development of targeted countermeasures. These measures could be successful at slowing, and in some cases even reversing any potential spaceflight associated brain changes, in a similar way to those that have been developed to counteract the effects of normal aging [56-59].

Cognitive and behavioral measures will be collected from astronauts before, during, and after spaceflight. Functional and structural brain scans will be obtained at multiple time points pre- and post-flight. A group of individuals that are participating in an ongoing head down tilt bed rest study, and a group of ground-based control subjects, will also complete the exact same assessments.

This is the first prospective longitudinal study assessing both spaceflight induced functional and structural brain changes and their relationship to sensorimotor and cognitive functioning.

### Objectives

The aim of our studies are to a) identify changes in brain structure and function that occur with spaceflight and prolonged bed rest and characterize their recovery time course; b) assess whether and how these changes impact behavioral and neurocognitive performance; and c) parcel out the contribution of microgravity to the potential brain functional and structural changes.

### Hypotheses

We hypothesize that measures of brain structure, function, and network integrity will change from pre to post flight in crewmembers, and to a lesser extent in bed rest participants with accumulating time, but not in control subjects. Moreover, we predict that these changes will correlate with indices of cognitive, sensory, and motor function in a neuroanatomically selective fashion.

## Design/methods

To investigate the effects of long-duration spaceflight on brain function and structure, we will perform an extensive neuro-imaging protocol, including task-based BOLD (blood oxygenation level-dependent) Magnetic Resonance Imaging (MRI), resting state functional connectivity MRI, high-resolution structural MRI, and diffusion weighted MRI. Potential demographic confounders will be collected for all subjects.

### Design

The current study includes three groups for which each the design is single group with repeated measures. Thus, astronauts and bed rest study subjects will serve as their own controls from pre flight to in flight and post flight test points, and pre bed rest to in bed rest and post bed rest respectively (see Table 1). In addition, the bed rest study will serve as an experimental analog for spaceflight because extended exposure to a head-down tilt position can duplicate many of the effects of a low-gravity environment [60]; thus, the study will consist of both within subject and between subjects comparisons.

**Table 1 T1:** Testing timeline for astronauts and bed rest subjects

**Astronauts**	**Pre launch**					**Flight day**						**Return**	
**Day:**	**-180**	**-90**				**30**	**90**	**150**				**+90**	**+180**
**Bed rest subjects**	**Pre bed rest**		**In bed rest**						**Post bed rest**				
**Day:**	**-12**	**-7**	**7**	**30**	**65-70**				**+0**	**+8**	**+12**		
**Behavioral measures**													
Thurston's card rotation task	X	X	X	X	X					X	X	X	X
Cube mental rotation task	X	X	X	X	X	X	X	X		X	X	X	X
Rod and frame test	X	X	X	X	X					X	X	X	X
Digit symbol substitution task of the WAIS	X	X	X	X	X					X	X	X	X
Purdue pegboard test	X	X	X	X	X					X	X	X	X
Computerized dynamic posturography	X	X							X	X	X	X	X
Functional mobility test	X	X							X	X	X	X	X
**Structural neuro-imaging**													
High resolution T1‒weighted imaging	X	X	X	X	X					X	X	X	X
Diffusion tensor imaging	X	X	X	X	X					X	X	X	X
**Functional neuro-imaging**													
Functional connectivity MRI	X	X	X	X	X				X	X	X	X	X
VEMP	X	X	X	X	X				X	X	X	X	X
Dual task	X	X	X	X	X	•	•	•	X	X	X	X	X
Sensorimotor adaptation task	X	X	X	X	X	•	•	•	X	X	X	X	X
Spatial working memory task	X	X	X	X	X				X	X	X	X	X
Foot tapping	X	X	X	X	X				X	X	X	X	X

WAIS = Wechsler adult intelligence scale; MRI = Magnetic resonance imaging; VEMP = Vestibular evoked myogenic potential; ● = fMRI paradigms of which the behavioral measure is completed while in space.

Comparing longitudinal outcome measures (i.e. brain structure and function) in astronauts with those in bed rest subjects will provide insight into the mechanisms behind the potential effects of spaceflight on the brain.

To evaluate the stability and reliability of our behavioral and MRI measures over time, we will also run a parallel study with ground-based control participants testing across multiple time points.

#### Testing timeline

Astronauts will be assessed at nine time points: two assessments will take place before launch (approximately 180 days and 90 days before launch), three assessments will take place while in flight (approximately day 30, 90, and 150); and four assessments will take place post flight (approximately 1-4, 30, 90 and 180 days post flight) (see Table 1).

Bed rest subjects will remain in bed with their heads tilted down for 70 consecutive days. Behavioral measures and neuroimaging assessments will be obtained at seven time points: a) two measurements will take place approximately 12 and 7 days before bed rest; b) two measurements will take place at approximately 7 and 30 days in bed rest; and c) three measurements post bed rest: one on 65 days into a 70 day campaign as close to day 0 when the subject gets up from bed (for all measures except those requiring upright stance), day 0 of standing up from bed for tests requiring upright stance, day 8 and 12 after the subject stands up for all tests (see Table 1).

Ground-based control subjects will be completing the exact same measures as the astronauts at four time points, with a one-month interval between each consecutive pair of time points.

### Participants

#### Recruitment

##### Astronauts

Thirteen astronauts will be recruited from crewmembers designated to visit the International Space Station (ISS). All astronauts who are assigned to a mission are given an opportunity to participate in a number of studies. Astronaut subjects who agree to participate in the study and whose in- and post- flight schedules match the study time line requirements are recruited into the study.

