#### Ground-based control subjects

Thirteen control subjects will be recruited from the Test Subject Facility at the NASA Johnson Space Center. These subjects need to be age matched with our astronaut subjects and will be required to pass an Air Force Class III equivalent physical examination.

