#### Sample size calculation

To calculate the sample size for this study we used data from the Functional Mobility Test (FMT). The FMT was designed to evaluate an astronaut’s ability to complete challenging locomotor maneuvers similar to those encountered during an egress from a space vehicle following long-duration space flight [20]. To perform the FMT subjects walked at a self-selected pace through an obstacle course set up on a base of medium density foam. The foam provided an unstable surface that increased the challenge of the test. The 6.0 m × 4.0 m course consisted of several pylons and obstacles made of foam. Subjects were instructed to walk through the course as fast as possible without touching any of the objects on the course. FMT data were used to calculate the sample size as it is the only pre/post flight data currently available with the longest recovery times (~15 days). If the other tests that are used in this study are similar to the FMT in sensitivity to spaceflight, we would fully expect to reject H_0_ for all tests. For example, from FMT results on 18 long-duration international space station (ISS) subjects, we found the mean change in log transit times to be 1.68 log sec with a standard deviation of 0.60 log sec [20]. With such a large signal-to-noise ratio and normally distributed differences the power of the t-test against H_0_ is virtually 1.0, even with as few as 10 subjects. Even if an outcome has only half the sensitivity of the FMT to spaceflight, the power with 10 subjects would still be 0.975. However, it is also important to have enough subjects to accurately estimate the mean change. If the sensitivity of a test to spaceflight were similar to that of the FMT, it would take about 13 subjects to produce a coefficient of variation of 10% for the estimated mean change post flight with respect to preflight performance. Therefore, under the assumption that sensitivities are comparable, we will require 13 long-duration astronaut subjects. We plan to target 15 subjects so we have a reserve of 2 subjects to account for subject attrition.

By including at least as much bed rest participants and control group participants as astronauts, we will ensure enough power to detect potential changes over time for these populations too.

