The number of astronauts to be included in the current study is aimed at thirteen. Proper sample size calculation revealed this number should be sufficient to accurately estimate behavioral changes from pre- to post space flight. Nevertheless, the relatively small sample size hinders inclusion of multiple confounders in statistical models, and makes it difficult to detect small changes. However, considering the absolute small number of astronauts that participate in long duration space flight, the proposed sample size is reasonable in terms of power and feasibility.

The major strength of this study is its unique nature. No prior studies have examined the effects of spaceflight on the extent, longevity and neural bases of sensorimotor and cognitive performance in human subjects. This study integrates high priority research topics in NASA’s Human Research Program, which seeks to estimate the risk of impaired control of a spacecraft, associated systems, and immediate vehicle egress due to vestibular and/or sensorimotor alterations that are associated with spaceflight. Moreover, the current study addresses the health and performance of crewmembers in flight and post-flight, which is important from a well-being perspective as well as in light of success of space flight missions. The results should also prove informative regarding the adaptive capacity of brain and behavior.

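### The recruitment section enrols 13 astronauts, but the sample size section needs 13 after attrition and targets 15, so recruiting as written leaves no reserve.

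*Protocol article*

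**What the plan says.** Four places in the protocol article bear on group size.

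- **Recruitment, Astronauts:** "Thirteen astronauts will be recruited from crewmembers designated to visit the International Space Station (ISS"). The section mentions neither 15 nor a reserve, and does not say that thirteen means evaluable subjects.
- **Sample size calculation:** from earlier FMT data, "we found the mean change in log transit times to be 1.68 log sec with a standard deviation of 0.60 log sec". On that basis "it would take about 13 subjects to produce a coefficient of variation of 10% for the estimated mean change post flight", hence "we will require 13 long-duration astronaut subjects", provided other tests respond to spaceflight about as strongly as the FMT. Then: "We plan to target 15 subjects so we have a reserve of 2 subjects to account for subject attrition". The section closes by making the bed rest and control groups no smaller than the astronaut group.
- **Ground-based control subjects:** "Thirteen control subjects will be recruited from the Test Subject Facility at the NASA Johnson Space Center".
- **Discussion:** "The number of astronauts to be included in the current study is aimed at thirteen", a number that the text attributes to the sample size calculation.

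**The concern.** The sample size section separates two quantities: the number needed for the precision criterion (13) and the number to enrol so that this many remain (15). The recruitment section attaches the first number to the act of recruiting. Someone running enrolment from that section would stop at 13 with nothing in hand for attrition.

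What is at stake is the basis on which 13 was chosen. The sample size section regards 10 subjects as ample for power and moves up to 13 only so that the mean change is estimated accurately. Precision therefore fixes the number, and precision is what suffers if subjects are lost from a group of 13. The Discussion notes how few astronauts fly long missions, so a lost subject may not be easy to replace.

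The ambiguity carries over to the controls. Their size is tied to that of the astronaut group, and the text does not say whether the reference is the 13 required or the 15 targeted.

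**Working it through.** **Inputs, all from the sample size section:** mean change in log transit time 1.68; SD 0.60; criterion CV = 10% for the estimated mean change; 13 required; 15 targeted; reserve 2.

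**Step 1: reproduce the stated 13.** The CV of a mean of n differences is (SD / mean) / √n. Setting this to 0.10 gives

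n = (0.60 / 1.68 / 0.10)² = (3.571)² = 12.76, rounded up to 13.

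The plan's figure reproduces, and 15 − 2 = 13 agrees with it.

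**Step 2: CV by number of evaluable astronauts.** With 0.60 / 1.68 = 0.3571:

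| Evaluable n | How reached | CV = 0.3571 / √n |
|---|---|---|
| 15 | 15 recruited, none lost | 9.2% |
| 13 | 15 recruited, 2 lost; or 13 recruited, none lost | 9.9% |
| 12 | 13 recruited, 1 lost | 10.3% |
| 11 | 13 recruited, 2 lost | 10.8% |

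With 15 recruited, the criterion survives two losses. With 13 recruited, it does not survive one.

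**Step 3: power.** The plan states: "Even if an outcome has only half the sensitivity of the FMT to spaceflight, the power with 10 subjects would still be 0.975". Half sensitivity means a standardised change of (1.68 / 0.60) / 2 = 1.4. The section gives no significance level or sidedness; I assume two-sided 0.05. A paired t-test, using the noncentral t distribution, gives 0.975 for n = 10, as stated. The same calculation gives 0.986 for n = 11 and 0.996 for n = 13.

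**Step 4: what the reserve is worth (illustration only).** The protocol states no attrition rate. Assuming independent losses at a common rate, the chance of ending with at least 13 evaluable is:

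| Assumed loss rate | 13 recruited | 15 recruited |
|---|---|---|
| 5% | 0.51 | 0.96 |
| 10% | 0.25 | 0.82 |
| 2/15 = 13.3% | 0.16 | 0.68 |
| 20% | 0.05 | 0.40 |

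These rates are assumptions, not the plan's. Across the range, the two extra astronauts make a clear difference to whether the criterion is kept.

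**The case against.** The strongest reply is that the protocol does provide a reserve. The sample size section gives the requirement, the target and the reason for the gap, and a careful reader can take the whole as 13 needed and 15 sought. The recruitment section contains no rule to stop at 13. This explains what was probably meant, but it does not remove the conflict: that section says how many will be recruited, and its number is the one without the reserve.

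Other parts of the reply limit the point, and they stand:

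- **The Discussion.** A reader might count its thirteen as a second conflicting recruitment figure. It speaks of the number to be included and refers back to the sample size calculation, so it can equally be the required number. It needs a clarifying word and is not independent evidence of the contradiction.
- **Expected losses.** A reader might infer that the plan forecasts two losses. It holds two in reserve and gives no rate. Eleven evaluable is the case in which losses use up the whole allowance.
- **Controls.** A reader might conclude that 13 controls break the plan's own rule. That follows only if the 15 targeted are the reference; against the 13 required, the rule is met.
- **Bed rest.** The absence of a number for this group is detail that a condensed article may leave to the full protocol, and is not a fault here.
- **Size.** The plan says about 13, and the calculation is conditional on other tests matching the FMT's sensitivity. A change of under one percentage point in the CV is small beside that uncertainty.

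**Conclusion.** The inconsistency is real. The recruitment section enrols 13; the sample size section requires 13 and targets 15. If 13 are recruited, one loss takes the CV of the FMT mean change from 9.9% to 10.3%, and two losses take it to 10.8%, against a criterion of 10%. These figures rest on the plan's own mean and SD and on a simple mean of paired changes.

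The consequence is a modest loss of precision and the loss of the attrition reserve. A reader might infer that the study would be underpowered. The documents do not support that: on the plan's assumptions, power at half the FMT's sensitivity with 11 astronauts is about 0.986 (two-sided 0.05 assumed), above the 0.975 that the plan quotes for 10. Nor is there an arithmetic error, since every stated figure that was checked reproduces. The point deserves correction because the enrolment target should be one number, and the text now gives two.

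**What to change.** 1. **Recruitment, Astronauts:** state that 15 astronauts will be recruited in order to retain 13 evaluable, as the sample size section already commits.
2. **Discussion:** say that thirteen is the evaluable number.
3. **Ground-based control subjects and Sample size calculation:** say whether the control group is to be no smaller than the 13 astronauts required or the 15 targeted, and set the control number to match.
4. **If only 13 astronauts can be recruited:** delete the reserve statement and give the precision as a CV of 9.9% to 10.8% for 13 to 11 evaluable.

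Items 1 and 2 are text corrections with no new commitment, because 15 is already the stated target. Item 3 costs one clarifying sentence if the reference is 13, or two further controls (15 − 13) if it is 15. Item 4 costs nothing beyond stating the weaker precision openly.

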#### Bed rest subjects

The bed rest program is a framework designed by NASA that offers researchers from various backgrounds the possibility to study bed rest as an experimental analog for space flight because extended exposure to a head-down tilt position can duplicate many of the effects of a low-gravity environment [48,60]. Participants will be recruited through the bed rest facility located at the University of Texas Medical Branch (Galveston, TX) and will participate in several studies as long as they are not interfering with each other.

Bed rest subjects are aged 18-60 years and will be required to pass an Air Force Class III equivalent physical examination. Female subjects in this study will model those in the astronaut population for whom participation in space missions is not allowed during pregnancy. Therefore, for female subjects, a non‒positive result from a pregnancy test will be required prior to inclusion in the study and prior to each experimental session.

#### Ground-based control subjects

Thirteen control subjects will be recruited from the Test Subject Facility at the NASA Johnson Space Center. These subjects need to be age matched with our astronaut subjects and will be required to pass an Air Force Class III equivalent physical examination.

